### Interventions

2.4.

#### Prehabilitation group

2.4.1.

Patients assigned to the prehabilitation group will receive a prehabilitation program in conjunction with their usual preoperative care. The program will be provided by a multidisciplinary team consisting of physicians, rehabilitation therapists, nurses, and nutritionists. Patients will engage in a structured one-week prehabilitation program starting from their entry into the waiting list before selective surgery, both at home and after their hospital admission.

EXERCISE module will be composed of two sessions, namely aerobic exercise and resistance training. Aerobic exercise will require patients to walk or engage in stationary cycling for 30 min, which includes a 5-minute warm-up and cool-down activity at least three times per week. Resistance training, on the other hand, will use elastic bands for the upper and lower limbs, chest, and core muscles with ten repetitions per major muscle group for three days. Videos demonstrating the exercise routines will be sent to the mobile phones of patients and their accompanying family members during hospitalization. The intensity of each patient's exercise will be personalized based on their health status, exercise performance, and training response. The appropriate heart rate ranged will be within the range of (220 – age) × (50%–60%) and we will monitor the patient's heart rate and subjective perceived exertion [Borg rating of perceived exertion (RPE)] throughout the exercise using a wristband (Xiaomi Wristband 7, Xiaomi Technology Co., Ltd.).

NUTRITION interventions will consist of early screening for malnutrition and structured education to reduce fat-rich diets and increase high-quality protein uptake. Patients will be encouraged to consume healthy, high-protein diets including high-quality protein sources such as eggs, fish, lean meats, or dairy. The optimal suggested diet goals will be set at 1.5–2 g/kg/d of protein from routine food intake. To assess the daily protein intake, patients will be recommended to keep diet journals, record and take photos of their three daily meals, which will then be evaluated and guided by a nutritionist. Malnourished patients will be transferred to a face-to-face nutrition clinic, and high-protein oral nutritional supplement (ONS) servings will be provided daily.

PSYCHOLOGY intervention will involve a one-week brief mindfulness practice session, with 10 min of practice per day before sleep. This intervention will focus on breathing mindfulness and feelings, guided by an audio-mindfulness dialogue. Psychologists will introduce a short mindful breathing practice after patient allocation. Mindfulness guidance recordings will be sent to the patient's mobile phone, and the practice of mindfulness on breathing and feeling will be encouraged.

#### Control group

2.4.2.

Patients assigned to the control group will not receive any additional prehabilitation intervention. Instead, they will receive usual care, which will include a thorough admission assessment, education on inspiratory muscle training, breath exercises, coughing, online health education, counselling, and nutrition risk assessment.

### Outcomes

2.5.

The timeline for this study will be one week. Prehabilitation will be implemented one week before the surgery, and the follow-up period will comprise of the perioperative period until the patient's discharge from the hospital. The outcomes will be assessed at four different time points: before the intervention (T0), upon admission to the hospital (T1), before surgery (T2), and after surgery (T3, before hospital discharge). Table 1 shows the complete assessment timeline.

**Table 1 T1:** Overview of assessment.

Measurement	T0: baseline	T1: hospital admission	T2: 1 day before surgery	T3: after surgery (before hospital discharge)
6-minute walk distance (6MWD)	×	×	×	×
Preoperative anxiety (APAIS)	×	×	×	
Frailty (FFPC)	×		×	×
Nutrition risks (NRS2002)	×	×		
Prehabilitation experience (FSS)		×	×	
ICU delirium (CAM-ICU-7)				×
Postoperative delirium (4AT)				×
Health-related quality of life (EQ-5D-5l)	×	×	×	×
Length of ICU stay, days				×
Length of hospital stay, days				×
Length of mechanical ventilation, hours				×

**The primary outcome** was the change in functional capacity over time, measured as the difference in absolute change in 6-minute walk distance (6 MWD) between T0 and T2 (primary analysis), as well as between T0 and T3. In this regard, a change of 20 meters from the baseline was deemed significant, indicating either an improvement or deterioration. To conduct this evaluation, participants will be instructed to wear comfortable footwear and walk back and forth in a 20-meter stretch of hallway for 6 min, aiming to reach a point of exhaustion by the end of the exercise. The tests will be conducted under the supervision of a blinded assessor following a standardized procedure to minimize potential sources of error due to bias or different levels of encouragement.

**Secondary outcomes** will comprise preoperative readiness (preoperative anxiety, frailty, and preoperative nutritional risks), postoperative recovery (delirium, frailty, HRQOL, and length of hospital stay), and patient experience with the program. Preoperative anxiety will be evaluated based on the Amsterdam Preoperative Anxiety and Information Scale (APAIS), perioperative frailty will be assessed using the Fried Frailty Phenotype Criteria (FFPC), and preoperative nutritional risk will be screened using nutritional risk screening (NRS 2002). The Flow State Scale short version will be used to examine patient experience of prehabilitation. Delirium will be assessed using the Confusion Assessment Method of the Intensive Care Unit -7 (CAM-ICU-7) and the 4AT Rapid clinical test for delirium for every nurse shift. HRQOL will be assessed using the EuroQol 5 Dimension 5 Level (EQ-5D-5l). The postoperative lengths of ICU stay, hospital stay, and mechanical ventilation will be recorded.

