### Randomization and blinding

2.7.

Eligible patients will have an equal opportunity to be randomly assigned to either the prehabilitation group or the control group in a 1:1 ratio. Randomization will be performed via a computer-generated block scheme and the resulting group assignments will be placed in opaque envelopes with sequential numbering by an independent research assistant not involved in this study. The research assistant will open a concealed envelope to allocate patients to their respective group. The main interventionist, assessor, and statistician will remain unaware of the group assignments until the envelope is sealed. Due to the intervention's inherent nature, it will not be possible to mask the participants or healthcare professionals.

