### Data collection and management

2.8.

At the baseline interview after randomization, demographic and clinical characteristics will be collected, including age, sex, BMI, ASA physical status class, comorbidities such as diabetes, hypertension, and hyperlipidemia, and Charlson Comorbidity index. Laboratory test results and assessment outcomes will be obtained from patients' electronic medical records, including serum hemoglobin, NRS 2002, HYHA, main diagnosis, and EuroScore. Additionally, data on daily exercise amount and intensity, diet details, and duration of mindfulness will be collected using a bracelet (Xiaomi Wristband 7, Xiaomi Technology Co., Ltd.). The 6 MWD test will be performed and recorded by trained researchers at our institution after providing standardized instructions and demonstrations of the tests. Patient-reported questionnaires will be administered, and the outcomes will be recorded by trained researchers. During the prehabilitation period, message interviews will be sent to patients every day, and feedback on their daily prehabilitation performance will be documented. After the surgery, information on the surgery, duration of ICU stay, and postoperative recovery will be obtained from electronic records. Patient identity and personal information will remain confidential unless consent is provided. All collected data will initially be recorded in a paper-based case report form and then entered into a digital database by an independent investigator.

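### Section 2.7 declares all healthcare professionals unmaskable, but that reason ends at surgery; delirium, apparently scored by shift nurses afterwards, has no masking although much of it is achievable

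*Protocol article*

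**What the plan says.** All references are to the protocol article.

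- **Section 2.5, secondary outcomes.** Delirium belongs to the postoperative-recovery group. It is measured with CAM-ICU-7 and "the 4AT Rapid clinical test for delirium for every nurse shift". Table 1 schedules both scales at T3 only, that is, after surgery.
- **Section 2.8.** Trained researchers perform the walk test and record the questionnaires, but after surgery "information on the surgery, duration of ICU stay, and postoperative recovery will be obtained from electronic records".
- **Section 2.7, masking.** Owing to the nature of the intervention, "it will not be possible to mask the participants or healthcare professionals". The sentence has no limit by role or by time.
- **Section 2.7, allocation.** "The main interventionist, assessor, and statistician will remain unaware of the group assignments until the envelope is sealed".
- **Section 2.4.1.** "The program will be provided by a multidisciplinary team consisting of physicians, rehabilitation therapists, nurses, and nutritionists".
- **Section 2.5, primary outcome.** For the 6MWD, "The tests will be conducted under the supervision of a blinded assessor following a standardized procedure"; the stated purpose is to limit error from bias and from uneven encouragement.
- **Sections 2.2 and 2.5.** The programme runs for one week, at home and then in hospital, and all of it falls before surgery.

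**The concern.** The protocol recognises assessor bias and guards against it for the walk test. It does not extend that guard to delirium, which also depends on an observer's judgement. Instead it gives up masking for every healthcare professional, on a ground that applies only to those who deliver exercise, diet and mindfulness sessions before the operation.

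Followed as written, the plan allows a nurse who coached a patient before surgery to score that patient for delirium after it, knowing the arm. If such raters expect the programme to help, borderline findings may be called differently in the two groups, and a difference in delirium could not be cleanly attributed to the programme. What is at stake is the credibility of one secondary outcome, not the primary result.

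**Working it through.** The plan states no figure on this point, so there is none to reproduce. The check compares the sections with one another.

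**1. Who rates delirium?** Section 2.5 gives the scales and a per-shift frequency but no rater. Section 2.8 assigns the walk test and questionnaires to researchers and takes postoperative recovery from the electronic records. Per-shift assessment plus record extraction points to routine charting by ICU and ward nurses; one research assessor could hardly cover every shift. This is an inference.

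**2. Does the stated reason for not masking apply to them?** Section 2.7 rests on the nature of the intervention. By sections 2.2 and 2.5 the intervention is finished when surgery begins, and by Table 1 delirium is rated only at T3. No programme element described requires a postoperative nurse to know the arm. The reason holds for staff delivering the programme and lapses for staff who only rate afterwards.

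**3. Are the two groups of staff kept apart?** Section 2.4.1 puts nurses and physicians on the delivery team, and section 2.2 places part of the programme in hospital. Nothing excludes those nurses from scoring.

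**4. Is masking secured elsewhere?** The blinded assessor in section 2.5 stands in the 6MWD paragraph, where the tests referred to are walk tests. Section 2.7 keeps an assessor unaware only up to the sealing of the envelope. That describes concealment of the allocation and secures no masking when outcomes are rated.

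**5. Could it matter? An illustration, not an estimate.** The documents give no delirium incidence and no rater accuracy, so every input here is assumed except 76 per group (section 2.9). Let the true incidence p be the same in both arms, 15% to 35%, with sensitivity s and specificity c by arm. The rated proportion is

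q = p·s + (1 − p)·(1 − c).

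The chance of a false-positive result is that of the two-sided pooled two-proportion test at 0.05, evaluated at the two values of q.

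Worked case, p = 0.25, specificity 0.95 in both arms, sensitivity 0.85 (control) and 0.75 (prehabilitation):

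- control q = 0.25 × 0.85 + 0.75 × 0.05 = 0.250
- prehabilitation q = 0.25 × 0.75 + 0.75 × 0.05 = 0.225
- false-positive rate = 0.065

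| Assumed rating, control vs prehabilitation | False-positive rate over p = 15–35% |
|---|---|
| Equal: sensitivity 0.85, specificity 0.95 | 0.05 |
| Sensitivity 0.85 vs 0.75, specificity 0.95 in both | 0.057–0.075 |
| As above, specificity 0.93 vs 0.97 | 0.125–0.129 |
| Sensitivity 0.85 vs 0.65, specificity 0.93 vs 0.97 | 0.19–0.25 |

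With 66 per group (half of the 132 required before the attrition allowance), the last three rows become 0.056–0.072, 0.115–0.118 and 0.17–0.23. A mild rating difference does little; a larger one in both sensitivity and specificity does a good deal. Nothing in the protocol says which row applies.

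**The case against.** The strongest reply is that the rater is never named and that the masking sentence in 2.7 is the usual open-label statement. Nothing says that ICU nurses will be told the arm, or that the allocation is written in the clinical record or passed on at handover. Who scores each scale is detail that a condensed article may leave to the full protocol. The scales are structured, this is an open-label pilot, and unmasked patients can reveal their arm at any shift.

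Part of this stands. The rater is inferred, and masking could be only partial. The omission of a name would not by itself be a finding. But the point rests on something stated: 2.7 declares all clinical staff unmaskable, for a reason that by the article's own timeline no longer applies when delirium is scored.

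A reader might go further and infer three things that the document does not support:

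- **That length of stay is biased through discharge decisions.** The article gives no discharge rule and nothing linking staff knowledge of the arm to discharge.
- **That the trial's main postoperative results are compromised.** The T0–T3 change in 6MWD sits within the primary outcome and has a blinded assessor; delirium is one of several unranked secondary outcomes.
- **That the bias can be expressed as a relative risk.** If a share u of true cases is missed in one arm only, the apparent relative risk is 1 − u, which merely restates the assumption. Even 35% against 24.5% at 76 per group gives z of about 1.42 and p of about 0.16. Repeated assessment may also soften under-calling if a case is any positive shift, though the article does not define a case.

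**Conclusion.** The point holds in a limited form. The ground given in 2.7 for leaving healthcare professionals unmasked does not extend to those who rate delirium after surgery. As written, arm-aware staff, including nurses who delivered the programme, may score this observer-judged secondary outcome, and no masking is promised for it. Knowledge of the arm can bias the result; the document does not show that it will, and the amount cannot be derived from it.

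The conclusion assumes that shift nurses are the raters, which is the natural reading of sections 2.5 and 2.8 taken together. The exposure is largely, not wholly, avoidable: more so in ICU, less so on wards where programme sessions were held. The primary 6MWD analysis is untouched. Severity is low to moderate.

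**What to change.** In section 2.7:

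- Limit the statement that masking is impossible to participants and to staff delivering the preoperative programme.
- State that the allocation is not passed to ICU or ward staff who score CAM-ICU-7 and 4AT after surgery, and that patients are asked not to disclose it.
- Have both scales scored by nurses who did not deliver the programme.

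In section 2.5, name the delirium rater. In the trial report, label delirium as masked or unmasked according to what was achieved.

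The cost is a few sentences and an instruction to postoperative staff. The scales and assessment frequency stay the same and no staff are added, although rosters must keep programme nurses from scoring trial patients. The downside is that masking will be incomplete, especially on wards where preoperative sessions were given and with patients who mention their arm.

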### Recruitment

2.6.

Individuals who meet the eligibility criteria will be presented with a comprehensive overview of the study's aims and procedures by a cardiac rehabilitation therapist if they express an interest in participating. The initial appointment will be scheduled 10–14 days before their hospital admission. Written informed consent will be collected from all participants at the hospital preparation center before the completion of the study assessments.

### Randomization and blinding

2.7.

Eligible patients will have an equal opportunity to be randomly assigned to either the prehabilitation group or the control group in a 1:1 ratio. Randomization will be performed via a computer-generated block scheme and the resulting group assignments will be placed in opaque envelopes with sequential numbering by an independent research assistant not involved in this study. The research assistant will open a concealed envelope to allocate patients to their respective group. The main interventionist, assessor, and statistician will remain unaware of the group assignments until the envelope is sealed. Due to the intervention's inherent nature, it will not be possible to mask the participants or healthcare professionals.

### Data collection and management

2.8.

At the baseline interview after randomization, demographic and clinical characteristics will be collected, including age, sex, BMI, ASA physical status class, comorbidities such as diabetes, hypertension, and hyperlipidemia, and Charlson Comorbidity index. Laboratory test results and assessment outcomes will be obtained from patients' electronic medical records, including serum hemoglobin, NRS 2002, HYHA, main diagnosis, and EuroScore. Additionally, data on daily exercise amount and intensity, diet details, and duration of mindfulness will be collected using a bracelet (Xiaomi Wristband 7, Xiaomi Technology Co., Ltd.). The 6 MWD test will be performed and recorded by trained researchers at our institution after providing standardized instructions and demonstrations of the tests. Patient-reported questionnaires will be administered, and the outcomes will be recorded by trained researchers. During the prehabilitation period, message interviews will be sent to patients every day, and feedback on their daily prehabilitation performance will be documented. After the surgery, information on the surgery, duration of ICU stay, and postoperative recovery will be obtained from electronic records. Patient identity and personal information will remain confidential unless consent is provided. All collected data will initially be recorded in a paper-based case report form and then entered into a digital database by an independent investigator.

### Sample size

2.9.

We determined that a difference of 20 meters in the change in 6-minute walk distance (6 MWD) between T0 and the T2 (primary analysis) in the prehabilitation group compared to the control group was a meaningful clinical outcome based on a previous study (22). Consequently, we conducted a sample size calculation using G*Power (version 3.1.) for the repeated-measures ANOVA with an alpha error of 5% and power of 0.95, with two groups and four measurements. The estimated sample size required was 132 patients. To account for a 15% attrition rate during the intervention period, the target sample size was increased to 152 participants (76 per group).

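### The 132-patient calculation is for a four-measurement repeated-measures ANOVA, not for the 20 m T0–T2 difference named as primary, so 95% power for the primary analysis is not established

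*Protocol article*

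**What the plan says.** Section 2.5 (Outcomes) defines the primary outcome as the between-group difference in absolute change in 6-minute walk distance (6MWD) "between T0 and T2 (primary analysis), as well as between T0 and T3". The comparison labelled primary therefore uses two of the four assessments.

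Section 2.9 (Sample size) takes as its meaningful effect "a difference of 20 meters in the change in 6-minute walk distance" from T0 to T2, prehabilitation against control, and again labels it the primary analysis. As a consequence of that target it reports a G*Power 3.1 calculation "for the repeated-measures ANOVA with an alpha error of 5% and power of 0.95, with two groups and four measurements". The result is given as "The estimated sample size required was 132 patients", and the target is raised to 152 (76 per group) for 15% attrition.

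Section 2.9 does not print an SD of 6MWD or of its change, a correlation between visits, a standardised effect, or which of G*Power's repeated-measures tests was chosen. Section 2.10 (Statistical analysis) plans a repeated-measures ANOVA for the primary outcome without naming the term to be tested.

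**The concern.** The target is one between-group contrast of two time points. The calculation offered for it is a four-visit ANOVA. With two groups and four measurements, the tests that involve group are:

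- the group main effect, which compares means averaged over T0, T1, T2 and T3 and so includes a baseline visit at which randomised groups should not differ;
- the group-by-time interaction, a 3-degree-of-freedom omnibus test of any difference in profile.

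Power for either is not power for the T0–T2 contrast, and nothing printed shows how 20 m leads to 132.

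The interpretation of the result is at stake. If the T0–T2 comparison is null, a reader who takes 95% at face value will treat it as strong evidence against a 20 m benefit. Whether that is justified depends on an SD the article does not give.

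**Working it through.** **Inputs from the article.** Difference 20 m in the T0–T2 change; alpha 0.05; power 0.95; 2 groups; m = 4 measurements; N = 132 (66 per group); 1:1 allocation.

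**Assumed, because not printed.** Effect size f, between-visit correlation ρ, test option, SD of 6MWD, and a two-sided 5% level for the contrast.

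**Step 1. Reproduce 132** (noncentral F, as in G*Power).

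Between-factors: λ = f²·N·m / (1 + (m − 1)ρ), with df 1 and N − 2.

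- f = 0.25, ρ = 0.5: λ = 0.0625 × 132 × 4 / 2.5 = 13.2. Power is 0.9501 at N = 132 and 0.9472 at N = 130, so 132 is the smallest even N.
- f = 0.20, ρ = 0.2: λ = 0.04 × 132 × 4 / 1.6 = 13.2. Same λ, so same N.

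Group-by-time interaction: λ = f²·N·m / (1 − ρ), with df 3 and 3(N − 2).

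- f = 0.10, ρ = 0.7: λ = 0.01 × 132 × 4 / 0.3 = 17.6. Power is 0.953 at N = 132 and just under 0.95 at N = 130.
- f = 0.25, ρ = 0.5: needs only N = 36, so this pair of inputs does not give 132 under the interaction.

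The printed figure is thus reproducible, but not from a unique set of inputs.

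**Step 2. Power for the T0–T2 contrast under those settings.** Two-sample t-test on the change score, 66 per group, noncentrality 20 / (SD_change × √(2/66)), with SD_change = SD × √(2(1 − ρ)).

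| Setting | How 20 m is read | SD | SD of change | Power, T0–T2 change |
|---|---|---|---|---|
| Between, f = 0.25, ρ = 0.5 | 2f = 0.5 SD | 40 m | 40 m | 81.4% |
| Between, f = 0.20, ρ = 0.2 | 2f = 0.4 SD | 50 m | 63.2 m | about 44% |
| Interaction, f = 0.10, ρ = 0.7 | group differences 0/0/20/20 m at T0–T3 | 50 m | 38.7 m | about 84% |

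Third row: the differences depart from their mean of 10 m by −10, −10, +10, +10. Half of each falls to each group, so the root mean square is 5 m, and 5/50 = 0.10.

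In the first row, 95% would need 105 per group. If T2 is instead adjusted for T0, the residual SD is 40 × √(1 − 0.5²) = 34.6 m and power with 66 per group is about 91%.

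**Step 3. What the between-factors test would detect** (first row). The SD of a patient's four-visit mean is 40 × √(2.5/4) = 31.6 m. The test has 95% power for an average difference of 20 m. If a 20 m effect is absent at T0 and present at T1–T3, the average is 60/4 = 15 m and power is 77%. If it is present at T2 only, the average is 5 m and power is 15%.

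**Step 4. Without any reconstruction.** For 20 m, two-sided 5%, change score:

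| Assumed SD of change | Power, 66 per group | Total N for 95% |
|---|---|---|
| 25 m | 99.5% | 84 |
| 30 m | 96.7% | 120 |
| 35 m | 90.3% | 162 |
| 40 m | 81.4% | 210 |
| 50 m | 62.6% | 328 |
| 60 m | 47.6% | 470 |

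The break-even SD of change for 95% with 132 patients is about 31.6 m, a standardised difference of 20/31.6 = 0.63.

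**The case against.** The best defence is that Section 2.10 does plan a repeated-measures ANOVA, so sizing and analysis belong to the same family, and that a condensed article need not print every G*Power entry. The first part stands as far as it goes. However, Sections 2.5 and 2.9 both single out T0–T2 as primary, and Section 2.10 names no term that would connect the ANOVA to that contrast. The second part excuses missing detail but not a mismatch between the stated target and the stated calculation.

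Three stronger readings are tempting, and the article does not support them.

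- **That 20 m never entered the calculation.** The article is silent. The f = 0.25, ρ = 0.5 match is suggestive, but the interaction setting can be built from a 20 m effect at T2 and T3 with an SD of 50 m.
- **That 95% is reached only if the groups already differ at baseline.** This applies to the between-factors option with the effect capped at 20 m at every visit. A larger later effect, such as 0/26.7/26.7/26.7 m, also averages 20 m, and the interaction option needs no baseline difference.
- **That the trial is shown to be underpowered.** Without an SD this cannot be shown. An SD of change of 31.6 m or less gives at least 95%. Even an SD of 40 m at a single visit with ρ = 0.7 gives an SD of change of 31.0 m and about 96%.

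It is also fair to say that 81% is for an unadjusted change score and that baseline adjustment recovers much of the gap (about 91%, same inputs). But Sections 2.5 and 2.9 define the outcome as a change, and 91% is still not the stated 95%.

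**Conclusion.** The mismatch is certain from the text: the calculation is not for the contrast it is said to serve, so 95% power for the primary analysis is not established.

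The size is conditional. Under the most conventional settings that reproduce 132, with f = 0.25 read as 20 m = 0.5 SD, power for the T0–T2 change is about 81%, or about 91% with baseline adjustment. That those settings were used is an inference; two other round-number settings also give 132 and imply different values. The statement that needs no reconstruction is the threshold: 95% on the change score with 132 patients requires an SD of change of about 31.6 m or less. All SDs used here are assumptions, not figures from the article. The finding is that the claim is unsupported, not that it is false.

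**What to change.** Keep the target of 152. In Section 2.9, replace the G*Power sentence with a calculation for the between-group T0–T2 contrast: 20 m, two-sided 5%, with a stated and sourced SD of 6MWD and T0–T2 correlation (or SD of the change). Use the same analysis as the primary test, either change score or T2 adjusted for T0, and name that test in Section 2.10. Report the power this N delivers in a short table over plausible SDs, and withdraw the unqualified 95%.

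The cost is a rewording plus the work of sourcing an SD and correlation. The fix itself asks for no extra patients and no change of design. The downside is that the stated power may become less favourable.

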**Methods and analysis:**

A single-center, parallel-group randomized controlled trial will be conducted at the Second Affiliated Hospital of Zhejiang University School of Medicine (SAHZU). A total of 152 adult patients scheduled for elective cardiac surgery (coronary artery bypass grafting or valvular surgery) will be recruited from a tertiary teaching hospital. The patients will be randomly assigned to either the control group or the prehabilitation group. Patients assigned to the control group will receive standard care, which includes patient education and counseling as well as personal guidance on exercise, breathing, and coughing. Patients in the intervention group will be provided a multimodal prehabilitation program, including nutrition guidance, a diet journal, mindfulness training, and exercise guidance. The interventions will begin with home-based training and continue after hospital admission and before surgery. The primary outcome will be the perioperative 6-minute walk distance (6 MWD). The secondary outcomes will include preoperative readiness, postoperative recovery, and patient experience with the program.

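### The target of 152 covers about 13% attrition, not the stated 15%: losing 15% of 152 leaves about 129 evaluable patients, against 132 required (minor)

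*Protocol article*

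**What the plan says.** All the inputs stand in section 2.9 (Sample size) of the protocol article.

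- The method is described as a "sample size calculation using G*Power (version 3.1.) for the repeated-measures ANOVA". Its settings, in the same sentence, are given as "with an alpha error of 5% and power of 0.95, with two groups and four measurements".
- The number that this calculation returned is reported in these words: "The estimated sample size required was 132 patients".
- The allowance for losses then reads: "To account for a 15% attrition rate during the intervention period, the target sample size was increased to 152 participants (76 per group").

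The abstract repeats the total ("A total of 152 adult patients scheduled for elective cardiac surgery") without mentioning attrition. The article does not give the formula that leads from 132 to 152, and it states no other attrition rate.

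**The concern.** An allowance for attrition is meant to ensure that, after the expected losses, the number that carries the stated power is still there. The losses come out of the patients randomised, so the required number has to be divided by the proportion retained. Multiplying it by one plus the attrition rate gives a smaller target, which falls short at the very rate it was meant to absorb. The figures in section 2.9 show this pattern.

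What is at stake is whether the sample-size statement is true as written: at the protocol's own attrition rate, its own target does not deliver its own evaluable number.

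**Working it through.** **Inputs (section 2.9).** Required number 132, which is 66 per group at 1:1 allocation; attrition 15%; target 152, or 76 per group.

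**Step 1. Reproduce the stated target.**
- Total: 132 × 1.15 = 151.8, rounded up to 152.
- Per group: 66 × 1.15 = 75.9, rounded up to 76.

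Both match. The multiplication is inferred from this match, since the article does not state it.

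**Step 2. Apply the stated attrition to the stated target.**
- Total: 152 × (1 − 0.15) = 129.2.
- Per group: 76 × 0.85 = 64.6.
- Shortfall: 132 − 129.2 = 2.8, about 3 evaluable patients.

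**Step 3. Find the target that retains 132.**
- Total: 132/(1 − 0.15) = 155.3, rounded up to 156.
- Per group: 66/0.85 = 77.6, rounded up to 78.
- Check: 156 × 0.85 = 132.6, which meets 132.
- Difference from the plan: 156 − 152 = 4 randomised patients.

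**Step 4. Find the attrition that 152 does cover.** (152 − 132)/152 = 20/152 = 13.2%.

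**Step 5. Effect on power.** The article gives no Cohen's f, standard deviation or correlation, so this step rests on assumptions. For the between-groups F test with m = 4 measurements, the noncentrality is λ = f²·N·m/(1 + (m − 1)ρ). With assumed f = 0.25 and ρ = 0.5, λ = 0.0625 × 4 × N/2.5 = 0.1·N, on 1 and N − 2 degrees of freedom.

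| Evaluable N | λ | Power |
|---|---|---|
| 132 | 13.2 | 0.950 |
| 129 | 12.9 | 0.946 |

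Under these assumptions 132 is the smallest even total that reaches 0.95, so they reproduce the protocol's number. The loss is about half a percentage point.

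**Step 6. Cross-check on the 20 m difference.** This is a two-sample comparison of the T0–T2 change, with 66 against 64.6 per group, over a range of assumed standard deviations.

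| Assumed SD (m) | Power at 66 | Power at 64.6 | Loss (points) |
|---|---|---|---|
| 25 | 0.996 | 0.995 | 0.1 |
| 31.9 | 0.950 | 0.946 | 0.4 |
| 40 | 0.819 | 0.811 | 0.8 |
| 50 | 0.632 | 0.623 | 0.9 |
| 60 | 0.482 | 0.474 | 0.8 |

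The loss due to the shortfall stays below 1 point throughout. The table says nothing about which standard deviation is right.

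**The case against.** The best defence of 152 is that 15% was meant as a margin on the required number, since 20/132 = 15.2%. On that reading the arithmetic is sound. But the sentence describes a rate at which patients are lost, and such a rate applies to those enrolled. The defence explains where 152 comes from without making the sentence correct.

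A second objection is that the gap is too small to matter: 4 randomised patients, and under half a point from a planned power of 0.95. That stands as a judgement of weight, and it is why the point is minor. It does not make the statement true.

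A reader might also infer that the shortfall is larger because the allowance covers only the intervention period while the sizing uses four measurements, the last after surgery. The article does not support that step. Sections 2.5 and 2.9 both name T0–T2 as the primary analysis, Table 1 places T2 one day before surgery, and the intervention runs in the week before surgery, so the allowance matches the primary contrast. No loss rate for T3 is given. Whether patients without a T3 value would be dropped depends on missing-data handling, which may sit in an analysis plan that is not shown.

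**Conclusion.** The point holds and is minor. At 15% attrition, 152 randomised patients leave about 129 evaluable, not 132; 152 covers about 13% attrition, and 156 would be needed to keep 132. This depends only on three figures in section 2.9 (132, 15% and 152) and on reading attrition as a proportion of those randomised.

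The size of the consequence does rest on assumptions. Power moves from 0.950 to 0.946 under f = 0.25 and ρ = 0.5; these values reproduce 132 but are not the protocol's stated setting. A reader might infer that the trial is underpowered because of this step, or that it must recruit more patients. Neither follows: the loss is under 1 point in every setting examined, and the design can stay as it is.

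**What to change.** Keep 152 and reword the last sentence of section 2.9 in one of two ways:

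- 152 patients (76 per group) allow for about 13% attrition from the 132 required; or
- with 152 patients randomised and 15% attrition, about 129 are expected to be evaluable.

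If a power is quoted for 129, it should come from the inputs actually used in the original calculation, not from the assumed values above. The cost is one sentence, with no extra patients and no change to the abstract. If the sponsor prefers to keep both 132 and 15%, the target becomes 156 (78 per group), which means 4 more patients and a matching change to the total in the abstract; the size of the effect does not require this.
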